### Participants

Potentially eligible participants will be approached at the participating university hospitals (outpatient clinic, inpatient units, and day clinic) by their treating psychiatrists. Furthermore, our study project was presented in local print media. In addition, potential participants could find relevant information on the trials homepage [24]. Finally, board certified psychiatrists were provided with the necessary information by mail as well as in the context of continued medical education training at our hospital. Eligible participants for this trial meet diagnostic criteria for Bipolar Disorders I or II and they can be either symptomatic or asymptomatic at time of enrollment (DSM-5: 296.4×; 296.5×; 296.89). At time of randomization, participants have to be remitted (DSM-5: 296.45, 296.46; 296.55, 296.56; 296.89). Further inclusion criteria consist of (1) age > 18 years, (2) signed informed consent prior to enrollment, (3) ≥ 3 affective episodes in last 5 years, one of them being a (hypo) manic episode, (4) smartphone usage, (5) and each patient must have a sufficient level of understanding to agree to all tasks required by the protocol. Exclusion criteria are comprised of (1) participation in another clinical intervention trial for the last 4 weeks prior to enrollment, (2) substance or other disorders that prevent the patient to understand the nature and consequences of the clinical trial, (3) signs that the patient will probably not comply with the study protocol (e.g. lack of cooperativeness), (4) current substance use disorder (except for tobacco and caffeine), moderate or severe, at enrollment, (5) borderline personality disorder, antisocial personality disorder, (6) dementia, organic brain disorders, (7) patients with a physical illness that probably requires inpatient treatment for more than 4 weeks per annum (exclusion: bipolar disorder), (8) patients working in a shift system which does not ensure regular night sleep, (9) relatives or persons in relation of dependence to study personnel, (10) women of childbearing age, excluding women meeting the following criteria: post-menopausal, postoperative (6 weeks after ovariectomy), regular and correct use of a contraceptive method, sexual abstinence or vasectomy of partner, (11) pregnancy or nursing.

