### Study procedure

Inpatients and outpatients with bipolar disorder I/II (currently symptomatic or stable) are assessed for eligibility by experienced clinical staff working at the study site who will present all relevant information about the background, design, procedure, etc. of the study to the patient and obtain informed consent in case of given eligibility. After having signed informed consent, a pseudonymized file is created for the patient in the electronic database and the movisensXS smartphone application is installed on a study smartphone handed over to the patient for his or her time of study participation, or, if wished, on the patient’s own device. Participants continuously receive open, guideline-based treatment for potential current (hypo)manic and depressive symptomatology for up to 20 weeks at the study sites outpatient clinics. As soon as stabilisation criteria are met (Young Mania Rating Scale total score < 12 and Inventory of Depressive Symptomatology, clinician version total score < 18) during four consecutive weeks, a baseline of the persons individual smartphone usage pattern during euthymia is automatically defined. Having fulfilled randomization criteria (four consecutive weeks with YMRS total score < 12 and IDS-C30 total score < 18), patients are randomly assigned to the Smartphone-Based Ambulatory Assessment group, including real-time data capture and data-driven therapeutic interventions (SBAA+), or to the Smartphone-Based Ambulatory Assessment group, only including real-time data capture (SBAA).

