### Statistical analysis

#### Confirmatory analysis

The primary objective (i.e. comparison of time to a new episode under SBAA+ vs SBAA) will be addressed with survival analysis. Kaplan-Meier plots will be used for estimating the survival functions; a Log-Rank test will be used to formally compare time to a new episode across treatment groups. By using this strategy, the analysis will include data from all patients who were randomized (ITT analysis). Although randomization will be used to attain comparable conditions at baseline in both groups, imbalances with respect to major confounders cannot be completely ruled out. In this case, the predefined survival analyses will be backed up by a Cox-regression which includes these confounders. All patients who have been randomized will be included in the statistical analyses.

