### Sample size calculation

Required sample size was calculated as in: *n* = 360 to be assessed for eligibility; *n* = 180 to be allocated to trial; *n* = 120 to be randomised to SBAA+ or SBAA; *n* = 120 to be analysed. The sample size of *n* = 60 per group was based on a power calculation for survival analysis with constant hazard and drop-out rates. This power calculation requires specific assumptions regarding (a) drop-out rate in SBAA (placebo), (b) global drop-out rate and (c) hazard ratio. Drop-out rate in SBAA (Placebo) was calculated with data from the psychiatric outpatient clinic, as this population most closely corresponds to the examined sample. Accordingly we expect a monthly hazard rate of 6%, which is equivalent to a relapse rate of 62% for the course of the trial. From our experience with comparable patients in similar studies we expect a drop-out rate of approximately 2.5%. This is equivalent to a drop-out rate of 26% for the course of the trial. A hazard ratio of 0.5 is estimated, according to a reduction of the relapse rate from 62 to 41% in the intervention group. This assumption is consistent with results of a Cochrane review on interventions, helping patients to identify early warning signs. The hazard ratio of 0.5 equals the median hazard ratio in studies, which compare TAU and TAU plus detection of EWS for relapse. This estimation is considered rather conservative as smartphone usage in this trial expectedly leads to a quicker and more reliable detection of warning signs, thus we expect a greater effect compared to the studies mentioned. Hence, with 81% this trial is sufficiently powered to demonstrate the advantage of SBAA+ compared to SBAA regarding the primary outcome (α = .05, one-tailed). Power calculation was performed using SAS software, version 9.3 (2011, Cary, NC).

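### The primary log-rank test leaves out pre-randomisation symptom scores that every randomised patient has; covariates fixed in advance could add a few points of power at almost no cost

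*Protocol article*

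**What the plan says.** All places are in the protocol article.

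- **Confirmatory analysis.** The formal test is unadjusted: "a Log-Rank test will be used to formally compare time to a new episode across treatment groups". If randomisation leaves imbalance on major confounders, "In this case, the predefined survival analyses will be backed up by a Cox-regression which includes these confounders". The confounders are not named, and the trigger is an imbalance seen in the data.
- **Study procedure.** Randomisation requires "four consecutive weeks with YMRS total score < 12 and IDS-C30 total score < 18". Design and study setting schedules weekly assessments before randomisation. Each randomised patient therefore has repeated totals on both scales.
- **Participants.** Entry requires at least "3 affective episodes in last 5 years, one of them being a (hypo) manic episode", so episode history is assessed for everyone. The article gives only this threshold and does not say that an exact count is recorded.
- **Randomization and blinding.** Allocation is stratified by age and bipolar type within site. Symptom scores and episode history are not randomisation factors.
- **Sample size calculation.** The size of "60 per group was based on a power calculation for survival analysis with constant hazard and drop-out rates" ("α = .05, one-tailed"). The conclusion is "Hence, with 81% this trial is sufficiently powered".

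**The concern.** The plan treats covariate adjustment only as a remedy for chance imbalance. In a time-to-event comparison, adjusting for baseline values that predict the event raises power even when the arms are balanced. When patients in an arm differ in relapse risk, high-risk patients relapse first, and they do so faster in the control arm. An unadjusted comparison then sees a hazard ratio closer to 1 than the effect within patients of similar risk. Adjustment recovers part of that difference.

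The Background describes the course of bipolar disorder as highly variable between patients. Entry also admits both symptomatic and asymptomatic patients, with 4 to 20 weeks before randomisation, so some spread in risk is plausible. With about 54 expected events, the plan is only just above 80% power. A few points available without more patients are worth having. A Cox model whose covariates are chosen after imbalance has been seen cannot serve as a pre-specified analysis.

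**Working it through.** **Step 1. Reproduce the stated power.**

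Inputs from Sample size calculation: n = 60 per arm, control hazard λ = 0.06 per month, hazard ratio 0.5 (so 0.03 in SBAA+), one-sided α = 0.05. Drop-out is 2.5%, read as monthly, so δ = 0.025. Follow-up is T = 18 months.

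Event probability per arm = λ/(λ+δ) × [1 − exp(−(λ+δ)T)]

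- SBAA: 0.06/0.085 × [1 − exp(−1.53)] = 0.553
- SBAA+: 0.03/0.055 × [1 − exp(−0.99)] = 0.343
- Expected events: 60 × (0.553 + 0.343) = 53.7 (unrounded inputs)

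Power (Schoenfeld) = Φ(√53.7/2 × ln 2 − 1.645) = 81.5%.

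Hazards back-calculated from the stated 62% relapse and 26% drop-out, with hazard ratio 0.5, give 53.0 events and 81.0%. The stated 81% reproduces either way.

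**Step 2. Let patients differ in risk.**

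Assumptions, not in the document: patient hazards within an arm are log-normal, with log-hazard SD 0.5, 0.75 or 1.0, and one baseline score explains 25%, 50% or all of that spread. Each setting has 3000 simulated trials (Monte Carlo error about 0.7 points), 60 per arm, with a one-sided 5% test. Each cell shows the power of the unadjusted log-rank test, then that of the adjusted Cox test.

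*Reading A: 0.5 is the hazard ratio within patients of equal risk, and control 18-month relapse is held at 66% (1 − exp(−0.06 × 18)).*

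| SD | 25% explained | 50% explained | all explained |
|---|---|---|---|
| 0.5 | 76.9 → 78.1 | 75.5 → 77.9 | 76.5 → 81.3 |
| 0.75 | 71.2 → 73.5 | 72.2 → 76.2 | 70.4 → 81.5 |
| 1.0 | 65.1 → 68.0 | 63.6 → 70.3 | 62.8 → 83.0 |

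Under this reading, relapse in SBAA+ rises to 43.7%, 45.8% and 48.0% at the three SDs. The log-rank test loses power because the group difference itself shrinks.

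*Reading B: the group-level 18-month risks are held at 66% and 42%, as implied by 0.06 and 0.03 per month.*

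| SD | 25% explained | 50% explained | all explained |
|---|---|---|---|
| 0.5 | 83.6 → 84.0 | 81.9 → 84.5 | 83.4 → 87.3 |
| 0.75 | 83.1 → 84.4 | 82.7 → 87.8 | 83.6 → 92.3 |
| 1.0 | 85.3 → 87.5 | 84.0 → 89.4 | 83.8 → 95.9 |

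Here the log-rank test stays at 82–85%. The within-patient hazard ratio that produces these group risks is 0.467, 0.431 and 0.390.

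**Step 3. Size of the gain.**

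At 25–50% explained, the gain runs from 0.4 points (84.0 − 83.6, reading B, SD 0.5) to 6.7 points (70.3 − 63.6, reading A, SD 1.0). The all-explained column is a ceiling, because it assumes a score that captures every difference in risk.

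**Step 4. Cost if the covariates predict nothing.**

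With no spread in risk, the simulation gives 80.7% for the log-rank test and 80.0% for the adjusted test. A separate simulation with three covariates also put the loss under 1 point, with one-sided type I error between 4% and 6%.

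**Step 5. Can 54 events carry the model?**

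Treatment plus three covariates: 53.7/4 = 13.4 events per parameter. Adding bipolar type and age as one term each: 53.7/6 = 9.0.

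**The case against.** The strongest reply is that nothing here is wrong. The log-rank test is valid, it matches the power calculation, and that calculation reproduces. A supportive Cox regression is already planned, and an analysis plan that is not shown may name its covariates. All of that stands, so the point is graded as inefficiency. What remains is a choice that the article does fix: the confirmatory test is unadjusted, and adjustment is both conditional on imbalance and secondary.

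The reply on prognostic value also largely stands. The article nowhere says that IDS-C30, YMRS or episode count predicts relapse. Both scores are truncated at randomisation (YMRS below 12, IDS-C30 below 18), which limits what they can explain. An exact episode count is not shown to exist.

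A reader might go further and infer from the constant-hazard wording ("was based on a power calculation for survival analysis with constant hazard and drop-out rates") that 81% is reached only if all patients in an arm share one hazard. The document does not support this. Log-rank power depends on the group-level event curves, and the plan's inputs are group-level: a clinic-population hazard, relapse percentages per arm, and a median hazard ratio across studies. With the group risks held, power stays at 82–85% under wide variation between patients. It falls to about 76–64% only if 0.5 is read as a within-patient hazard ratio, which the article does not state.

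**Conclusion.** The point holds as a recommendation for a more efficient primary analysis. The stated 81% stands, and the planned test is valid. Pre-specified adjustment would add about 0–7 points of power under either reading of the hazard ratio of 0.5, if baseline values explain 25–50% of a log-hazard SD of 0.5–1.0. It would cost under 1 point if they explain nothing. The SD and the explained share are both assumptions. Given the range restriction of the symptom scores, the upper end should not be counted on. The case rests on the balance of a possible modest gain against a negligible loss, and on replacing an imbalance-triggered model with one fixed in advance.

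**What to change.** Before outcomes are examined by arm, state in the confirmatory analysis that the primary comparison is the treatment term of a Cox model with named covariates:

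- the last IDS-C30 total before randomisation;
- the last YMRS total before randomisation;
- the number of affective episodes in the last five years, if an exact count is recorded (otherwise omit it);
- ideally also the randomisation factors bipolar type and age.

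Keep the Kaplan-Meier curves and the unadjusted log-rank test as supportive, and remove the imbalance trigger. The change costs a paragraph of wording and needs no extra patients or visits. The one item to confirm is whether the episode count is in the database. The small downside is that the hazard ratio becomes conditional on the covariates, so the unadjusted one should be reported beside it.

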#### Explorative analysis

Regarding secondary endpoints, separate survival analyses will be applied according to the variables level of measurement. For continuous endpoints, means and standard deviations respectively medians and quartiles are applied (graphically according to confidence intervals respectively boxplots), for categorical endpoints absolute and relative frequency are applied. Depending on the distribution of the analyzed variables, a *t*-test, *U*-test and *Chi*^2^-test are applied. For intraindividual comparisons a paired *t*-test is applied for normally distributed variables, and a Wilcoxon-test for not normally distributed variables.

Access to the final trial dataset is granted to the sponsor who is the owner of all data. Access is also granted to biometry staff.

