**Methods/design:**

The current study is designed as a randomized, multi-center, observer-blind, active-control, parallel group trial within a nationwide research project on the topic of innovative methods for diagnostics, prevention and interventions of bipolar disorders. One hundred and twenty patients with bipolar disorder will be randomly assigned to (1) the experimental group with included automated feedback or (2) the control group without feedback. During the intervention phase, the psychopathologic state of all participants is assessed every four weeks over 18 months. Kaplan-Meier estimators will be used for estimating the survival functions, a Log-Rank test will be used to formally compare time to a new episode across treatment groups. An intention-to-treat analysis will include data from all randomized patients.

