#### Outcomes

Primary outcome of this trial is time to new affective episode, defined by DSM-5 criteria for depressive, manic or hypomanic episode. The primary outcome will be determined by SCID I section A (for DSM-IV, additional DSM-5 question for energy/activity being included), criteria for current depressive and (hypo) manic episode, in monthly assessments during the intervention phase. The primary outcome is clinically highly relevant to determine the affective and mental stability of bipolar patients.

Secondary endpoints are (1) time to a new depressive episode, (2) time to a new (hypo) manic episode, (3) time to a new affective episode defined by DSM-5 but with modified time criterion of ≥ four days of episode duration, (4) percentage of assessments during intervention phase at which the original DSM-5 criteria for an affective episode are met, (5) percentage of assessments during intervention phase at which the modified DSM-5 criteria for an affective episode are met. These outcomes will also be determined by SCID I section A (for DSM-IV, additional DSM-5 question for energy/activity being included), criteria for current depressive and (hypo) manic episode, in monthly assessments during the intervention phase. Further secondary outcomes are (6) percentage of assessments during intervention phase at which criteria for an affective episode, defined by YMRS (> 12) and IDS-30 (> 18) score are met and (7) average severity of manic and depressive symptoms at assessments during intervention phase. These criteria are estimated by total YMRS and IDS-C30 scores at every assessment. Operationalization of the secondary outcomes (8) percentage of assessments during intervention phase at which the patient was hospitalized for an affective episode, and (9) percentage of days during intervention phase at which the patient was hospitalized for an affective episode, is self-explanatory. (10) Number of adverse events is measured by the SAE (serious adverse event) reporting form included in the electronic case report form (eCRF).

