### Randomization and blinding

A randomization list is stored in the electronic database where all collected data is entered using eCRFs. Based on this list, patients are allocated to the two groups (SBAA resp. SBAA+) by block randomization, stratified by age and type of bipolar disorder (I or II) for every study site. Pseudonymized files are created in the database for enrolled patients. The system allocates patients to the groups corresponding to the stored algorithm for randomization and the required stratification factors. The patient and the assigned psychiatrist are automatically and instantly informed about which group (SBAA vs. SBAA+) the patient was allocated to once randomization is carried out via the database system. As regular ratings must not be biased by group allocation knowledge, the observer/rater remains blinded. Both treating psychiatrist and patient are asked explicitly not to disclose any information allowing conclusions regarding group allocation. As the study psychiatrists are not blinded, there was no need to provide special procedures for emergency unblinding.

The intervention phase is planned for 18 months (72 weeks). During this time, state-of-the-art treatment of the bipolar condition continues for both groups. Attending psychiatrists will receive automatic feedback from the movisensXS feedback server, every time the previously calculated individual thresholds of patients in the SBAA+ group are significantly exceeded in any direction. A standardized procedure follows, where the psychiatrist contacts the patient to assess, whether (a) the changes in smartphone usage patterns can be explained by external circumstances, or (b) show no hint for the beginning of a new affective episode (false alarm), or (c) the changes result from early signs of bipolar episodes. In this case treatment options are discussed with the patient as in regular guideline-based treatment. Additionally, in the case that the rater detects an affective episode, the study clinician will be informed so that thresholds can be changed towards more sensitivity if the patient is enrolled in the intervention group and no automatic alarm has been present.

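### The exploratory percentages and average scores are compared by unadjusted tests that weight a short early follow-up like a full one and use neither baseline scores nor strata; a repeated-measures model would be a cheap, optional improvement

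*Protocol article*

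**What the plan says.** In the Protocol article, the Outcomes section defines endpoint 4 as the "percentage of assessments during intervention phase at which the original DSM-5 criteria for an affective episode are met". Endpoints 5, 6 and 8 take the same form for other criteria, endpoint 9 is a percentage of days in hospital, and endpoint 7 is the "average severity of manic and depressive symptoms at assessments during intervention phase". The abstract gives the visit schedule: "the psychopathologic state of all participants is assessed every four weeks over 18 months". With a 72-week intervention phase (Randomization and blinding), that is 72 / 4 = 18 assessments.

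The Explorative analysis section names the comparison: "Depending on the distribution of the analyzed variables", a t-test, U-test or chi-square test. It gives no weighting, repeated-measures model or covariate. The only adjusted model is the Cox regression in the Confirmatory analysis section, which backs up the survival analyses if an imbalance appears.

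The trial nevertheless holds useful covariates. YMRS and IDS-C30 are scored over four weeks before randomisation (Study procedure), and allocation is "stratified by age and type of bipolar disorder (I or II) for every study site".

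**The concern.** A percentage or mean over attended visits depends on how long the patient stayed. Everyone is randomised in remission, so early visits should show fewer episodes than later ones. A patient who leaves early contributes a value that is both noisier and drawn from the low-risk start of follow-up, and a t- or U-test counts it like a completer's value. If one arm loses more patients early, that arm can look better with no treatment effect. Differential drop-out is conceivable because patients know their allocation and only SBAA+ patients are contacted after alarms.

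Unadjusted tests also leave unused the precision that baseline scores and strata could give. The Outcomes section expects the secondary endpoints to show how robust the primary result is, so an avoidable artefact or loss of precision there is worth removing.

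**Working it through.** **The plan's own figures.** No precision or power is stated for these endpoints. The relevant stated input is drop-out: "we expect a drop-out rate of approximately 2.5" per cent, read here as monthly (assumption), and 26% over the trial. With hazards of 0.06 and 0.03 and drop-out d = 0.025 over 18 months, the share leaving before a first episode is d/(h+d) × (1 − exp(−(h+d) × 18)):
- control: 0.294 × (1 − exp(−1.53)) = 23.0%
- intervention: 0.455 × (1 − exp(−0.99)) = 28.6%
- average: 25.8%, which matches the stated 26%.

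The percentage endpoints run over the whole intervention phase, so overall drop-out is what matters here, and it is higher.

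**Number of assessments.** With 28-day visits (0.92 month) and exponential drop-out at 2.5% per month:
- fewer than 18: 1 − exp(−0.025 × 0.92 × 18) = 33.9%
- four or fewer: 1 − exp(−0.025 × 0.92 × 5) = 10.9%
- none: 1 − exp(−0.025 × 0.92) = 2.3%, about 3 of 120.

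Counting 18 monthly steps instead, 1 − 0.975^18 = 36.6% (43.9 of 120) have fewer than 18. If 26% is taken as total drop-out, the figures are 31.2 of 120 with fewer than 18 and about 2 with none.

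**Cost of equal weights.** With within-patient correlation ρ (assumed), the variance of a mean of k visits is proportional to ρ + (1 − ρ)/k. A one-visit value then has 1/(ρ + (1 − ρ)/18) times the variance of an 18-visit value: 6.7 at ρ = 0.1, 4.1 at 0.2, 3.0 at 0.3, 1.9 at 0.5. At 2.5% monthly drop-out, equal weighting keeps 84%, 92%, 96% and 99% of the efficiency of inverse-variance weighting.

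**Bias under no effect.** Assume prevalence rises linearly from 5% at visit 1 to 25% at visit 18, identically in both arms. The expected percentage over the first k visits is 5 + (20/17)(k − 1)/2: 5.0 for k = 1, 6.8 for k = 4, 15.0 for k = 18. Averaging over the distribution of k among patients with at least one visit:

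| Monthly drop-out by arm (assumed) | Expected percentages | Difference |
|---|---|---|
| equal | equal | 0 |
| 2% vs 3% | 13.51 vs 12.87 | −0.64 points |
| 1.5% vs 3.5% | 13.85 vs 12.58 | −1.27 points |

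Simulation with 60 per arm and a patient random intercept (SD 0 to 1 on the logit scale, assumed) gives a standard error of about 2 to 3 points. The two-sided t-test rejects in about 6% of trials at 2% vs 3% and in 7 to 11% at 1.5% vs 3.5%. Simply pooling visits still leaves −0.29 and −0.58 points; the bias goes only when visit time is in the model.

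A second simulation used a monthly two-state process (onset 6%, recovery 25% to 50%, assumed). Drop-out of 2.5% vs 5% shifted the percentages by 0.4 to 1.1 points. When patients in one arm left at 10% per month while in an episode, against 2.5% otherwise, the shift was 0.6 to 1.1 points. In that last case pooled visits did worse at 25% recovery: 14.7% vs 16.6%.

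**Choice of test.** In the two-state process at 33% recovery with no effect, false-positive rates were 5.1% (t), 4.9% (U) and 4.9% (chosen after a normality check). The percentages were non-normal in every run, so the check always led to the U-test.

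**Baseline adjustment.** The variance removed is r²: 9% at r = 0.3 and 25% at r = 0.5 (r assumed). The entry limits (YMRS below 12, IDS-C30 below 18) restrict the baseline range and may hold r down.

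**The case against.** These analyses are labelled explorative and only the log-rank test is confirmatory. A mean of per-patient percentages is a legitimate patient-level summary, and equal weighting costs at most 8% of efficiency once ρ is 0.2 or more. The bias needs both differential drop-out and rising prevalence. The sample size section assumes one global drop-out rate and a constant hazard, and gives no support for either condition. All of this stands, and it limits the point to an optional improvement.

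Three stronger readings are tempting, and the document supports none of them.
- A reader might infer that picking the test from the data inflates false positives. The simulated rates stay at 5%.
- A reader might see a contradiction with "All patients who have been randomized will be included in the statistical analyses", since a percentage over zero visits is undefined. That sentence closes the Confirmatory analysis section and follows the survival methods. Handling of patients without assessments in exploratory endpoints may sit in the full protocol or SAP.
- A reader might fear a chi-square test on pooled assessments, which ignores clustering and gave 30% false positives in the simulation. The section mentions categorical endpoints just before and nowhere says that visits would be pooled.

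What remains is that the article names specific unadjusted tests for repeated-measures data, although a better method needs no new data.

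**Conclusion.** The point holds as an optional improvement to the exploratory analyses. The named t- and U-tests give short, early follow-up the same weight as full follow-up, and baseline scores and strata are unused. About 34% of patients would have fewer than 18 assessments (26% to 37% depending on how the drop-out figure is read). The loss of efficiency from equal weights is 1% to 16% for ρ between 0.5 and 0.1. Bias is about 0.6 to 1.3 points under the assumed unequal drop-out and rising prevalence, well inside a standard error of about 2 to 3 points, and is zero with equal drop-out and no effect. Prevalence, drop-out by arm, ρ and r are assumptions; the document gives none of them. The primary test and its conclusion are untouched.

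**What to change.** In the Explorative analysis section, replace the tests for these endpoints with one prespecified model each:
- **Endpoint 7:** a mixed model for repeated measures with arm, visit, arm-by-visit, baseline YMRS or IDS-C30, site, age group and bipolar type.
- **Endpoints 4, 5, 6 and 8:** a mixed logistic model on visit-level status, or GEE with drop-out weights, with arm, visit time (categorical or smooth) and the strata, clustered by patient. Visit time has to be in the model. Unweighted GEE would not handle drop-out that depends on earlier episodes.
- **Endpoint 9:** hospital days per four-week interval, with interval as a factor. A single total with a log(days) offset assumes a constant rate and would keep the early low-risk bias.

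Report estimates with 95% confidence intervals. State how many randomised patients have no post-randomisation assessment; they contribute no outcome data under either approach.

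The cost is revised wording and slightly more programming, with no new data. Model-based estimates need more explanation than raw percentages, which can still be tabulated descriptively.

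### If the planned paired tests are run on YMRS or IDS-C30 against the pre-randomisation value, they start from scores selected to be low and are not evidence on SBAA+

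*Protocol article*

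**What the plan says.** Under Explorative analysis, the protocol article fixes two kinds of test for continuous data. Between groups: "Depending on the distribution of the analyzed variables, a *t*-test, *U*-test and *Chi*^2^-test are applied". Within patients: "For intraindividual comparisons a paired *t*-test is applied for normally distributed variables, and a Wilcoxon-test for not normally distributed variables". Neither carries a baseline adjustment, and the second does not say what is paired with what.

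Study procedure sets the score condition for randomisation: "four consecutive weeks with YMRS total score < 12 and IDS-C30 total score < 18". Patients may enrol while symptomatic and have open treatment "for up to 20 weeks at the study sites outpatient clinics" in which to reach it. Participants adds: "At time of randomization, participants have to be remitted". Sample size calculation plans for 180 patients allocated to the trial and 120 randomised.

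The same two scales return as a secondary endpoint under Outcomes: "average severity of manic and depressive symptoms at assessments during intervention phase". That is an average over the phase, not a change from baseline.

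**The concern.** The trial has parallel groups and no crossover, so a within-patient pair must be two time points. YMRS and IDS-C30 are rated repeatedly, and a comparison with the pre-randomisation value is a natural use of the sentence. That value has passed a filter: only low scores lead to randomisation. Later scores carry no such filter, and they also include the episodes that the trial exists to count. A rise from baseline is thus possible in both arms with no effect of the feedback.

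What is at stake is interpretation. A reader shown a significant rise in SBAA and a non-significant one in SBAA+ may take this for a treatment effect, although no comparison of the arms has been made.

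**Working it through.** **1. The plan's own figure.** Sample size calculation gives 60 per arm, a control hazard of 0.06 per month, a hazard ratio of 0.5 (so 0.03 in SBAA+), drop-out of 2.5% (read as monthly, d = 0.025), one-sided α = 0.05 and 81% power; follow-up is 18 months.
- Expected events per arm = 60 × h/(h+d) × (1 − exp(−18(h+d))).
- SBAA: 60 × 0.06/0.085 × (1 − exp(−1.53)) = 33.2. SBAA+: 60 × 0.03/0.055 × (1 − exp(−0.99)) = 20.6. Total 53.7 (before rounding).
- Schoenfeld power = Φ(√53.7 × ln 2 / 2 − 1.645) = 81.5%.

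The stated 81% reproduces and owes nothing to the paired tests.

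**2. Sensitivity of a paired test with 60 patients.** For a mean change of δ standard deviations of the change, and an assumed two-sided 5% level, the chance of a significant rise is about Φ(δ√60 − 1.96):

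| δ | 0.1 | 0.2 | 0.3 | 0.4 | 0.5 |
|---|---|---|---|---|---|
| chance | 12% | 34% | 64% | 87% | 97% |

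So the question is how large a shift selection and relapse produce.

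**3. Selection alone (simulated, no relapse, no feedback effect).** IDS-C30 is stable around each patient's own mean, and entry needs four consecutive weekly scores below 18 within 20 weeks. Means, SDs and autocorrelation are assumptions, since the article gives none. Chance of significant worsening in one arm of 60:

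| Assumed usual IDS-C30 mean | Phase average | Last visit |
|---|---|---|
| 14 to 18 | 98–100% | 79–99% |
| 10 | 31–55% | 20–33% |
| 6 | 3–4% | 2–3% |

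In one run at mean 18, the phase average rose by 4.86 points with an SD of 6.28, so t = 4.86/(6.28/√60) = 6.0. At mean 6 the cut-off hardly selects and there is no inflation.

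**4. Relapse alone (simulated).** Baseline and euthymic follow-up scores come from the same distribution, so only episodes move the mean. Assumptions: patient mean about 8 (SD 3.5), visit-to-visit SD 3, episode scores about 30 (SD 8), mean episode duration 2 or 3 months, and all or half of the episodes depressive.

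| Monthly hazard | Mean rise in phase average (points) | Phase average significant | Last visit significant |
|---|---|---|---|
| 0.06 (SBAA as planned) | 1.2–3.1 | 72–100% | 24–85% |
| 0.03 (SBAA+ as planned) | 0.6–1.7 | 28–89% | 8–44% |
| 0.015 | 0.3–0.9 | 12–44% | 5–16% |
| 0.0075 | 0.2–0.4 | 5–16% | 4–7% |

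**5. Two arms side by side.** If the feedback does nothing and each arm is significant with probability p, exactly one arm is significant with probability 2p(1 − p). At hazard 0.06 in both arms:
- Phase average: 2 × 0.72 × 0.28 = 40% at the low end of p, and 0% at p = 1.
- Last visit: 2 × 0.85 × 0.15 = 26% at the high end of p, with the maximum of 50% at p = 0.5, which lies within the range.

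**6. Comparing the arms instead.** A t-test between arms on the same scores, under the models of step 3, had a false-positive rate of 4–6% throughout. The selection acts on both arms alike and cancels. Adjustment for the pre-randomisation score is therefore a matter of precision: it multiplies the residual variance by about 1 − r², where r is the within-arm correlation of baseline with the phase average. The article gives no r.

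**The case against.** The strongest reply is that the article never describes a before-after test of symptom scores. It speaks only of intraindividual comparisons. None of the ten secondary endpoints is a change from baseline, and other within-patient data exist, such as the eight smartphone parameters with individual baselines described under Intervention. The section is headed "Explorative analysis", between-arm tests stand beside the paired ones, and no conclusion about SBAA+ is attached to the latter. Which pair is meant may be settled in the full protocol. All of this stands, and it is why the point is conditional and minor.

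A reader might go further and infer that the paired tests are bound to show significant worsening whatever the feedback does. The documents do not support that. The chance falls to 2–4% if usual scores lie well below the cut-off, and it falls as the hazard falls, so it does depend on any effect of the feedback on relapse. Nor are patients admitted solely for low scores: diagnosis, smartphone use and "≥ 3 affective episodes in last 5 years, one of them being a (hypo) manic episode" also apply. Relapse after euthymia is real worsening, and a paired test that detects it describes the course of illness correctly. It simply does not say what the feedback contributed. YMRS was not simulated; for that scale only the reasoning carries over.

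What the reply does not remove is that a within-arm test of these scales cannot show an effect of SBAA+, however it turns out.

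**Conclusion.** The point holds in conditional form. Applied to YMRS or IDS-C30 against the pre-randomisation value, the paired tests start from scores selected to be low. They can signal worsening unrelated to the feedback and are not evidence on SBAA+. The size is open: about 2% to 100% per arm for IDS-C30, depending on the assumed usual mean, spread, episode pattern and hazard. At the sponsor's own control hazard the relapse model gives 72–100% on the phase average.

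The document does not plan to read a difference in within-arm significance as the treatment effect; that is a risk in reporting. The confirmatory log-rank test and its power are untouched. Removing every paired test would go too far, because it would also remove comparisons of variables that were not used for selection.

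**What to change.** For YMRS and IDS-C30 only:
- Report within-arm change from baseline descriptively, as a mean with confidence interval and without a test, and note that entry required low scores on both scales.
- Base any statement about SBAA+ on the between-arm difference in average severity during the intervention phase. Estimate it by ANCOVA with the pre-randomisation score as covariate, in place of the unadjusted *t*- or *U*-test. State beforehand which pre-randomisation rating is used.
- Say which variables and time points the intraindividual comparisons cover. Paired tests on variables other than these two scales need not change.

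The cost is a few lines of text. The pre-randomisation scores are already collected to establish eligibility, so no further patients or data are needed. What is lost is a set of within-arm p-values that do not address the trial's question. The gain in precision depends on the baseline correlation and may be modest, since selection narrows the range of baseline scores.
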